**Figure 2 figure2:**
[figure not shown]
CONSORT (Consolidated Standards of Reporting Trials) diagram for electronic medication administration record (eMAR) game pragmatic trial.

#### Phase 2

The specific questions to be asked during focus group interviews with participants will be informed by the preliminary quantitative findings [35]. Although emergent and contingent on the quantitative findings, it is expected that a range of qualitative interview questions will be developed based on the core variables in part 1 of the study (ie, medication errors generated, self-efficacy and knowledge related to administration, etc). During these focus group interviews, participant feedback related to the usability, design, and user experience of the game will also be sought. Approximately 20 participants from either semester (both intervention and control groups) will be interviewed in the qualitative phase of this study (week 9).

### Data Analysis

#### Phase 1

Survey data will be analyzed through descriptive and inferential statistics. Student *t* test to compare pre- versus postcontinuous outcomes for intervention and control groups in relation to number of medication errors or near misses, number of deviation from best practices, and length of time (efficiency) of administration will be completed.

#### Phase 2

Semistructured focus group interviews will be audio recorded and transcribed verbatim. A minimum of 2 researchers will conduct a directed content analysis [36] of the data; this will be triangulated with quantitative findings [37] to generate a deeper understanding of the effectiveness of the gamified eMAR simulation as a technology-enabled clinical education tool.

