
### Study Design

The primary study design (phase 1) will consist of a prospective, 2-armed pragmatic randomized controlled trial. Phase 2 will consist of qualitative focus group interviews, conducted after the completion of phase 1.

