### Setting and Recruitment of Participants

Two waves of second-year baccalaureate nursing student participants will be contacted and recruited for participation in this proposed study at the beginning of 2 separate academic semesters: wave 1 will commence in September 2017 (fall semester) and wave 2 in January 2018 (winter semester). Due to the size of the second-year nursing student cohort (N=150) and resource limitations of the CSL, only half (n=75) of the students will partake in simulated clinical education in the CSL, per semester (split between fall and winter). Inclusion criteria for this study will be (1) second-year nursing students and (2) partaking in clinical simulated education either in fall 2017 or winter 2018 semesters. Students recruited in this study will not have had previous exposure to medication administration, and this simulated clinical experience will be their first formative interaction with medication administration and the SMART eMAR.

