**Figure 1 figure1:**
[figure not shown]
Screenshot of the electronic medication administration record (eMAR) simulation game’s user interface and various player-manipulable objects.

Before the start of each term, a researcher-led presentation will be delivered outlining the proposed study purpose, methods, and study benefits. Given the typical student enrollment within second year of the BScN program, it is expected that approximately 150 students will fit this inclusion criterion and be eligible for recruitment into the study. Participants will be offered a Can $5 gift card for a coffee shop as a nominal incentive to participate in the study. Due to the high recruitment success rate experienced in the corresponding pilot study completed in April 2016 (25/27, 93% of students sampled) [11], we estimate 120 participants will be recruited. By including at least 120 participants, phase 1 of our study will be able to detect an intervention effect size of 0.25, with a power of 0.8 and a .05 level of significance, based on a 2-tailed *t* test analysis, as calculated by G*Power 3.1 (Heinrich-Heine-Universität Düsseldorf, Germany).

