### Data Collection

#### Phase 1

After recruitment and enrollment into the study (week 1), nursing students in each semester will be randomized into either the intervention or control group and will be assigned a unique participant code number. The allocation ratio will be 1:1 (intervention or control group), following a simple randomization procedure (Microsoft Excel [Microsoft Corp.] random number table). Research team members involved in data collection will be blinded to the allocation; participants will become aware of their randomization on receipt of an email from the researchers outlining their allocation into the intervention or control group. At this time, students in the intervention group will receive access to the eMAR simulation game approximately 2 weeks in advance of their in-person simulation sessions with the eMAR technology in the CSL. Along with access to the eMAR simulation game, students in the intervention group will also have access to other usual preparatory educational resources related to medication administration, such as a video demonstrating proper administration technique and a PowerPoint presentation on eMAR medication administration. To ensure a consistent duration of game intervention, students will be requested to use the eMAR simulation game for a minimum of 60 min (with no maximum) [29] before conducting their return demonstration of a medication administration using the actual SMART eMAR system in the CSL (starting week 5); analytics software operating in the background of the game will be used to track the average game play duration of participants. Students allocated to the control group will receive the usual preparatory resources related to eMAR medication administration, without access to the eMAR simulation game. At the conclusion of the trial in late October and February (week 9), all participants in the control group will receive access to the eMAR simulation game.

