#### Outcomes

Data will be collected by 4 data collectors (nursing graduate students with clinical backgrounds using eMAR technology) who will observe nursing student participants during their return demonstration of medication administration using the SMART eMAR (weeks 5-8). These data collectors will be trained by members of the research team before the study initiation to ensure the appropriate and consistent use of the checklist to collect participant data. Mock student return demonstrations and related data collection will be conducted to improve interrater reliability; Fleiss kappa coefficients will be calculated and used to further refine interrater reliability of the data collection procedure. A formalized checklist that has been developed and used previously in an adapted form by the research team [20] will be implemented as the primary data collection instrument for phase 1. This data collection checklist will capture the following quantitative data during each participant’s medication administration return demonstration using the SMART eMAR: (1) frequency of deviations from medication administration best practices, (2) number of actual medication errors or near misses generated by the student that violate the various medication best practices and provincial regulatory requirements related to medication administration [30,31], and (3) overall duration of time required by the student to complete the entire medication administration simulated scenario. Secondary outcomes using prepost survey data related to medication self-efficacy and knowledge will be collected using questions modified from previously developed and tested instruments [32,33]. Secondary outcome cross-sectional data will also be collected using questions modified from the Huang et al’s [34] validated instrument that measures motivational (ie, attention, relevance, confidence, satisfaction) and cognitive processing of learning in game-based environments (20 questions, Cronbach alpha=.91). Measurement of motivational and cognitive processes of learning will identify levels of participant motivation related to cognitive load requirements demanded by the eMAR simulation game.

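### The Phase 1 t test is written as pre versus post for errors, deviations and time, which are each recorded only once, so it cannot be run as worded

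*Protocol article*

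**What the plan says.** Study Design describes a "prospective, 2-armed pragmatic randomized controlled trial". Under Data Collection, students are randomised individually: "The allocation ratio will be 1:1 (intervention or control group").

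The Outcomes section says the checklist data come from observers "who will observe nursing student participants during their return demonstration of medication administration using the SMART eMAR (weeks 5-8"). The checklist yields three quantities per student: deviations from best practice, errors or near misses, and the time taken for the scenario. Setting and Recruitment of Participants adds that "this simulated clinical experience will be their first formative interaction with medication administration and the SMART eMAR".

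Repeated measurement is described only for the survey, in weeks 4 and 8. Outcomes refers to "Secondary outcomes using prepost survey data related to medication self-efficacy and knowledge".

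Data Analysis, Phase 1, then plans a Student t test "to compare pre- versus postcontinuous outcomes for intervention and control groups in relation to number of medication errors or near misses", with deviations and time in the same sentence. For the survey data it mentions descriptive and inferential statistics in general.

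The sample-size statement, under Setting and Recruitment of Participants, reads "By including at least 120 participants" the study "will be able to detect an intervention effect size of 0.25", with power 0.8, significance level .05 and a two-tailed t test. It does not say whether that test is paired or independent.

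**The concern.** A pre-post test needs two values per student. For the three checklist outcomes the article provides one. The method is therefore attached to outcomes that cannot supply its input, while the outcomes that are measured twice are not in the sentence.

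The first research question asks whether the game improves safety in simulated practice. Only a comparison of the two randomised groups answers it, and the one contrast written out is a different one. If the wording stands, the analyst must choose the real test later. The Results section says collection for the fall 2017 cohort has already concluded, so that choice could fall after data have been seen. The choice between a paired and an independent test also determines what the stated power means.

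**Working it through.** **1. Outcome by outcome**

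| Outcome | When measured (Data Collection, Outcomes) | Values per student | In the pre-post t test sentence? |
|---|---|---|---|
| Errors or near misses | Return demonstration, weeks 5-8 | 1 | Yes |
| Deviations from best practice | Return demonstration, weeks 5-8 | 1 | Yes |
| Time to complete | Return demonstration, weeks 5-8 | 1 | Yes |
| Self-efficacy, knowledge | Survey, weeks 4 and 8 | 2 | No |

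No section describes a checklist observation before the return demonstration. The statement that students have had no previous exposure to medication administration leaves no existing source for one. The test sentence and the measurement schedule do not fit together for any of the three outcomes it names.

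**2. The stated sample size under each reading of the test**

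Inputs from the article: N = 120, 1:1 allocation (120/2 = 60 per arm), effect size 0.25 (index not named), two-sided .05, power 0.80. Power is from the noncentral t distribution. The noncentrality is d × √(n/2) for two independent groups of n each, and dz × √N for a paired or one-sample test.

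| Reading | Noncentrality | Power at N = 120 | N for 80% power |
|---|---|---|---|
| Independent groups, d = 0.25, 60 per arm | 0.25 × √30 = 1.37 | 27.4% | 253 per arm, 506 in total |
| Paired or one-sample, dz = 0.25, all 120 | 0.25 × √120 = 2.74 | 77.5% | 128 |
| Independent groups, 0.25 read as Cohen's f, so d = 2 × 0.25 = 0.5 | 0.5 × √30 = 2.74 | 77.5% | 64 per arm, 128 in total |

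No reading gives exactly 120 at 80%. Two come close: a paired or one-sample test on all 120 students, and an independent test with 0.25 taken as f. The article does not say which was used.

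**3. What the between-arm comparison can detect**

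For an independent two-group test with 60 per arm, two-sided .05, the standardised difference detectable with 80% power is d = 0.52. That is 0.52/0.25 = 2.1 times the stated effect size, if 0.25 is a standardised mean difference. The article gives no standard deviation, so this cannot be expressed in errors or minutes.

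**The case against.** The best reply is that the intent is clear. The trial has two randomised arms, the test sentence names both groups, and the sample-size statement speaks of an intervention effect. On that reading a between-arm t test was meant and the pre-post clause is a slip. This largely stands: it would be wrong to say that the authors did not intend to compare the arms. It does not rescue the sentence, which names a specific method for specific outcomes that the schedule cannot support. This is therefore a contradiction in the article and not detail left to an analysis plan.

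A reader might infer more than the article supports:

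- *That no pre value could ever exist.* Lack of earlier exposure shows that none is planned or available. It does not show that a baseline observation would be impossible.
- *That the primary analysis is undefined.* No outcome is labelled primary. That status is inferred from the checklist being called the primary instrument and the survey outcomes secondary.
- *That the survey outcomes lack a test.* A condensed article may leave that to the fuller plan. It is not a fault here.
- *That the plan has a very high false-positive rate.* Suppose each arm were tested pre to post separately and efficacy were claimed when only the game arm was significant. With 60 per arm, no true arm difference and an assumed pre-post correlation of 0.5, exactly one arm is significant with probability 2p(1 − p), where p is the power of one paired test. This is 21%, 44%, 47% and 24% for common gains of 0.1, 0.2, 0.3 and 0.4 SD, but 9.5% with no gain and 6% at 0.5 SD. Half of each figure would favour the game. The article plans no such analysis of the survey scores, states no such reading rule, and gives neither the gain nor the correlation. The figures illustrate why within-arm tests should be avoided. They do not measure a defect in this plan.

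**Conclusion.** The Phase 1 analysis is wrong as written. A pre-versus-post t test is assigned to three outcomes that are each observed once, and the between-arm contrast that would answer the first research question is implied but never stated. This follows from the article's own sections and needs no outside assumption.

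The numerical consequence is conditional. If the test is stated as an independent two-group comparison and 0.25 is a standardised mean difference, 120 participants give about 27% power instead of 80%. This assumes an even 60/60 split, no dropout and a normal-theory t test. If 0.25 was Cohen's f, the power is 77.5%, close to the stated value. The article must say which index it used.

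**What to change.** - **Data Analysis, errors or near misses, deviations and time:** replace the pre-post wording with a comparison of intervention and control on the single return-demonstration value, by allocated group. Report the difference, or a rate ratio for counts, with a 95% confidence interval.
- **Data Analysis, self-efficacy and knowledge:** if the pre-post wording was meant for these, move it there as a between-arm comparison. The week-8 score adjusted for the pre-score is preferable on efficiency grounds, where that pre-score was taken before game access. A between-arm comparison of change from such a baseline is also valid. Do not use separate pre-post tests within each arm as evidence of efficacy.
- **Sample-size statement:** say that the t test is an independent two-group test, name the effect-size index, and restate the figure. With 60 per arm at two-sided .05 that is about 27% power at d = 0.25, or 80% power at about d = 0.52.

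Make these changes before any results by arm are examined. They need no new data, only new wording and acceptance of a less favourable stated power.

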### Ethics

Ethical approval for this study has been obtained from Western University, London, Canada (HSREB #109180).

## Results

Preliminary results of half of the desired study cohort is expected in early 2018. By early spring 2018, the findings of the study in its entirety will be available. Currently, data collection of the fall 2017 cohort has concluded.

## Discussion

### Principal Considerations

Due to the pragmatic randomized controlled trial design, the findings of this study will establish baselines regarding the effects of serious gaming approaches toward improving nursing students’ eMAR medication administration safety; similarly, the findings will also outline best practices toward the development of immersive gamified simulation opportunities that can be leveraged by other educational organizations. Given the lack of research and consolidated knowledge about this teaching-learning approach [38], both quantitative and qualitative findings arising from this study will provide important theoretical and pragmatic insights to others developing immersive simulation or virtual reality opportunities.

Although still an emerging area of research, there is growing interest toward the development of serious gaming or gamified approaches in clinical education [6,39,40]. Recent evidence suggests that gamified approaches in nursing education can offer a range of benefits, including anxiety reduction in students, improvement in the repeatability of skills, and increased access to learning opportunities [41,42]. Other nursing education research has posited that there is no difference between gamified learning versus face-to-face clinical simulation [43]. Medical education research has found largely positive results regarding the use of gamification as a teaching-learning mechanism, in terms of medical content validity [27], acceptance and retention of learned knowledge [44], and ongoing skill retention and learner engagement [29,45]. The growing importance and interest in this topic can also be inferred from the recent registration of a *Cochrane Database of Systematic Review* protocol, which plans to examine the effectiveness of serious gaming and other gamified interventions in health professional education [38]. As outlined by Cant and Cooper [41], this type of clinical education pedagogy will likely “have a major place in nursing curricula in the next decade,” and therefore warrants further examination by clinician educators.

### Strengths and Limitations

As a strength, this study will be one of the first appropriately powered trials of a serious gaming intervention in nursing education. Furthermore, the pragmatic randomized controlled trial design [46] with complementing qualitative elements will assist in generating informative insights related to the effectiveness of using a serious gaming intervention to educate students to the complexities of medication administration in an eMAR environment. Although this study has some strengths, there are some limitations that should be outlined. First, the observational method and environment for data collection raise the potential of an observer effect, in that participants may recognize they are being observed by members of the research team during their return demonstration of a medication administration scenario in the CSL. Second, the variability in data collection by multiple observers may be a potential limitation. Although standardized observation guides and training will be provided to the data collectors, interrater reliability between observers may be a source of study error. Finally, given the structure of the game, it is not possible to fully ascertain whether there is a dose-response relationship between cumulative gameplay time and its effect on medication error frequency rates. As the eMAR simulation game offers the player a fair amount of autonomy to make errors and experiment with different actions and processes, any linear relationship examined between overall gameplay time of a participant and their medication error rate may not be an accurate depiction of medication administration knowledge or comprehension.

### Conclusions

Given the potential severity of health outcomes caused by medication errors, nursing education continues to place emphasis on simulated clinical education to provide students with the necessary clinical skills related to medication administration before direct interaction with real patients. Simulation has been widely adopted within clinical education to support medication administration education. However, because of financial and resource constraints experienced by educational institutions, opportunities for students to meaningfully practice eMAR administration continue to be limited. The development of innovative clinical learning strategies such as serious gaming and gamification may offer new opportunities for students to learn these important skills and develop clinical judgment. The findings of this study will generate evidence of a gamified approach to learning in nursing education and provide new pedagogical implications to prepare students with the appropriate skills, knowledge, and competencies related to electronic medication administration.

## Appendix

Multimedia Appendix 1 Funder feedback.

## Abbreviations

CSL: clinical simulation laboratory
eMAR: electronic medication administration record
SMART eMAR: a physical, simulated eMAR system used within the university’s CSL
